### Blinding

Because the efficacy of acupuncture inevitably depends on the skill of the operating doctors, allocation concealment to the doctors is not feasible for trials on acupuncture. Consequently, we applied a single-blind design in which the patients are blinded to their allocation. The statisticians are blinded to all treatment allocations throughout the study.. The concealment will not be broken until the final data analysis report is completed.

During and intervention phrase, the participants are treated with tube-guided needles that have the same appearance as the treatment needles. Similarly, use of the seeds in the sham acupuncture group gives the patient the sensation of a needle being inserted. Both the genuine acupuncture points and the sham points are in similar locations on the patients’ neck, back, and hands, and the participants cannot observe the manipulation performed during the treatment, therefore, the blinding should be effective.The requirements for the treatment sessions (the duration and frequency) are the same. After the second session and at the end of the treatment, participants are required to complete a questionnaire to assess the blinding.

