### Sample size calculation

The size calculation is based on the mean and standard deviation (SD) for NPQ from a pilot study [1]. The reported pilot study was a two-arm design with a treatment group and one placebo group, whereas this trial protocol is a three-arm design with one treatment group (OAT) and two control groups (sham group and shallow group). The mean ± SD of the treatment group reported in the pilot study (20.71 ± S 11.91) [1] were used as the expected values of the OAT group, and the mean ± SD of the placebo group (24.04 ± 11.83) were used as the expected values of the two control groups. The software Power Analysis and Sample Size (PASS; version 11; NCSS Statistical Software, Kaysville, UT, USA) was used to perform the sample size calculation.

The sample size was calculated with a significance level of 0.05 and power of 0.90. The result was a total required sample size of 732, with 244 for each group. With a maximum dropout tolerance of 15%, 32 patients per center are needed for each group, or 94 patietns overall per center. Therefore, 846 patients are needed for the trial, with 288 for each group across the nine centers.

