### Statistical analyses

EpiData software (version 3.1 is used for data entry, and SPSS (version 16.0; SPSS Inc., Chicago, IL, USA) for statistical analyses. The analytic strategy includes the descriptive analysis of the demographic characteristics and the baseline data for the primary and secondary outcomes. The group differences are tested by analysis of variance (ANOVA) for continuous variables, the Kruskal-Wallis test for ranking variables, and the χ² test for categorical variables. The significance level is set at α = 0.05, two-sided.

There are four measuring points set to assess the efficacy of the OAT, as described above in the Outcomes section. Therefore, we will apply the two-factor repeated measures analysis of variance (ANOVA) model with the time of measure as the within-subjects factor and treatment as the between-subjects factor (significance level α = 0.05, two-sided). In addition, stratification analysis will be used to explore the potential effect difference between centres.

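### Centre is absent from the stated efficacy model of a nine-centre trial; adding it is nearly free and gains a little precision, and the exploratory centre analysis should be one interaction test

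*Protocol article*

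**What the plan says.** The Statistical analyses section names a two-factor repeated measures ANOVA for the outcomes, with measurement time within subjects and treatment between subjects. Neither factor is centre. The sentence that follows gives centre its only role: "stratification analysis will be used to explore the potential effect difference between centres". No centre-adjusted estimate and no treatment-by-centre test is named.

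Elsewhere centre is part of the design. Trial design lists nine hospitals in different regions of China. Sample size calculation plans recruitment by centre and arm: "32 patients per center are needed for each group". Blinding remarks that "the efficacy of acupuncture inevitably depends on the skill of the operating doctors". The Randomization section does not say whether allocation is stratified by centre.

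**The concern.** Two things follow from this wording.

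- **Precision.** If NPQ levels differ between hospitals, that variation stays in the error term of a model without centre. When the arms are balanced within centre, the treatment difference itself does not carry this variation. The model then reports a standard error larger than the true one, and some power is given away.
- **Interpretation.** The stated aim is to explore whether the effect differs between centres. A set of separate by-centre results does not answer that question; a treatment-by-centre interaction does. With about 30 patients per arm in a centre, by-centre p-values would look inconsistent even if the effect were the same everywhere. The article does not say which form the stratified analysis will take.

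**Working it through.** **Inputs** (Sample size calculation and Statistical analyses)

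- OAT arm: "treatment group reported in the pilot study (20.71 ± S 11.91"; both control arms: "the mean ± SD of the placebo group (24.04 ± 11.83". Difference 24.04 − 20.71 = 3.33; pooled SD √[(11.91² + 11.83²)/2] = 11.87.
- Alpha: "The significance level is set at α = 0.05, two-sided". Power 0.90.
- Centre share of NPQ variance, ρ: not given. Assumed range 1% to 10%.

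**1. The plan's own figure.** The section states: "The result was a total required sample size of 732, with 244 for each group". A three-group F test with means 20.71, 24.04 and 24.04 has Σ(μᵢ − μ̄)² = 7.39. At n = 244 and SD 11.91 the noncentrality is 244 × 7.39 / 11.91² = 12.7, and power is 0.900. The figure is reproduced. With 15% dropout, 244 / 0.85 = 287.1, taken as 288 per arm, or 288 / 9 = 32 per arm per centre.

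**2. Pairwise comparison without centre.** SE = 11.87 × √(2/244) = 1.075, and 3.33 / 1.075 = 3.10. Power ≈ Φ(3.10 − 1.96) = 0.873 (0.871 with the t distribution).

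**3. Effect of omitting centre when arms are balanced within centre.** The true SE is SE_w = 1.075 × √(1 − ρ), but the model reports 1.075.

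- True alpha = 2 × [1 − Φ(1.96/√(1 − ρ))]
- Unadjusted power = Φ[(3.33 − 1.96 × 1.075)/SE_w]
- Adjusted power = Φ[3.33/SE_w − 1.96]

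| ρ (assumed) | SE_w | True alpha, unadjusted | Power, unadjusted | Power, adjusted | Gain (points) |
|---|---|---|---|---|---|
| 1% | 1.069 | 0.049 | 87.4% | 87.6% | 0.2 |
| 2% | 1.064 | 0.048 | 87.5% | 87.9% | 0.4 |
| 5% | 1.047 | 0.044 | 87.9% | 88.9% | 1.0 |
| 10% | 1.020 | 0.039 | 88.5% | 90.4% | 1.9 |

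**4. Power within one centre.** Power ≈ Φ(3.33/SE − 1.96), with SE = 11.87 × √(2/m). At m = 32, SE = 2.97 and power is 0.201. With 32 × 0.85 = 27.2 completers, power is 0.177 (t test, m = 27: 0.173). The Discussion's total of 945 gives 945 / 27 = 35 per arm per centre and power 0.216 (t test 0.212). The range is 17% to 22%. At 0.20, about 9 × 0.20 = 1.8 of nine centres would reach p < 0.05 under one common effect of 3.33.

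**5. Power of the interaction test.** This takes OAT against one control over nine centres (8 degrees of freedom), where the true effects vary between centres with SD τ (assumed). For 27 to 35 per arm per centre, power is about 8% to 9% at τ = 1, 19% to 24% at τ = 2, and 48% to 59% at τ = 3.33.

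**The case against.** - **By-centre significance tests are not stated.** A reader might infer that the plan commits to nine separate tests with about 20% power. The text says only that stratification will be used to explore differences. That could equally mean centre-specific estimates, a homogeneity test or a pooled stratified estimate, and a condensed article may leave the form to a fuller document. This stands. The low per-centre power is a caution about interpretation in an analysis labelled exploratory. It bears on no confirmatory claim.
- **The gain is easily overstated.** A reader might set 87.3% against 88.9% or 90.4% and claim 1.6 or 3.2 points. That comparison ignores the fact that the unadjusted test also gains power when arms are balanced within centre, so it cannot be combined with the argument that standard errors are too large. Under balance the gains are 1.0 and 1.9 points.
- **The primary test remains valid.** A reader might infer bias or an inflated false-positive rate. Neither follows: under balance the error is conservative, and without stratified allocation the unadjusted test is still valid. This stands.
- **The remark on operator skill supports less than it seems to.** It explains why the doctors cannot be blinded. If skill changes efficacy, the result is a treatment-by-centre interaction, which a centre main effect does not absorb. This also stands.
- **The replacement test is weak too.** True, as step 5 shows. Its merit is that it is a single test aimed at the question asked.

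None of this removes the basic point: a model described as having two factors, both named, has no place for centre.

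**Conclusion.** The point holds as a small improvement at almost no cost. Centre is missing from the stated efficacy model although recruitment is organised by centre and arm. If allocation is balanced within centre, the unadjusted analysis is mildly conservative (true alpha 0.039 to 0.049), and adjustment gains about 0.2 to 1.9 power points over assumed centre shares of 1% to 10%.

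The size rests on three assumptions:

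- The centre share is unknown.
- Balance within centre is suggested by the planned equal numbers, but the Randomization section does not confirm it.
- The calculation is for a pairwise comparison at one visit, on the same means and SDs as the sample size. A centre difference that is constant over visits cancels from the time-by-treatment test, so the gain there would come only from centre differences in change over time.

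The documents support neither a biased primary result nor a commitment to underpowered by-centre tests.

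**What to change.** 1. In Statistical analyses, add centre as a between-subjects factor to the NPQ model and to the MPQ and SF-36 models.
2. Replace the sentence on stratification with a definition: one exploratory treatment-by-centre interaction test, with centre-specific treatment differences and confidence intervals. State that no separate significance tests will be made by centre, and that a non-significant interaction will not be read as proof of equal effects.

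The cost is wording, plus 8 degrees of freedom for the centre main effect out of 732 − 3 = 729. With three arms, the interaction takes 2 × 8 = 16 more, in the separate exploratory model only. No new data are needed. The article reports that recruitment is still under way and that the statisticians are blinded, so the change can still be prespecified.

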## Discussion

The objective of this trial is to evaluate the effect of the OAT scheme for neck pain in patients with CS. The first draft of the OAT treatment scheme was developed based on the practice and clinical experience of the Acupuncture Department of Guangdong Provincial Hospital of Chinese Medicine. The draft was then discussed by a special committee of Guangdong Association of Acupuncture and revised. The revised edition was submitted and reviewed by the national expert committee of acupuncturists organized by SATCM, and the final version of the OAT scheme was approved by the consensus of the committee.

The OAT scheme comprises two steps: the first step is classic acupuncture therapy at the nine standard points with de qi sensation for 20 minutes, and the the second step is the administration of INT in which the needles are fixed by medical tape. The treatment lasts for 4 weeks with eight to ten sessions at a frequency of two to three times per week. The overall effect of OAT is related to the duration and frequency of the treatment. The intradermal needles are an empirical method to maintain the pain-relieving effect of classic acupuncture, therefore, the treatment frequency of classic acupuncture can be reduced to twice per week. As a result, both the final outcome and patient compliance are improved.

For a high-quality RCT, use of the appropriate control is crucial. In this trial, two questions must be addressed. First, is the OAT treatment effective on CS neck pain? Second, does the OAT treatment have a superior effect to the control treatments in treating CS neck pain? The sham and shallow acupuncture groups were designed as control groups in this study to answer these questions.

Sham acupuncture is considered to be a placebo treatment in acupuncture studies. In general, sham acupuncture can be divided into two categories: non-penetrating and penetrating sham acupuncture, which is determined by whether the needle penetrates the skin during the intervention. According to the literature, there are four types of non-penetrating sham acupuncture in use: 1) skin touch on standard points or non-points [24,25], 2) blunt telescoping sham needle [26,27], 3) transcutaneous electrical stimulation [28], and 4) sham laser acupuncture [29,30]. It is reported the non-penetrating sham acupuncture has been applied as a placebo in numerous trials; however, it was also found that 40% of the subjects in these trials could distinguish the sham acupuncture from the real treatment [31], breaking the blind concealment. Therefore, we considered that non-penetrating sham acupuncture would not be a useful placebo for this trial. However, two types of penetrating sham acupuncture are also available: 1) non-point deep puncturing needle insertion [32,33] and 2) non-point superficial needle insertion [34,35]. Although skin penetration is believed to cause some therapeutic effect such as diminished pain intensity, it is considered non-specific, and can be caused by other interventions. The greater the insertion depth and the more stimulation induced by the needle, the greater the effect. Consequently, we chose to usethe non-point superficial needle-insertion method for the trial. The needles are inserted into the sham points to a depth of 3 mm and are retained at the subcutaneous level. Because the needles are inserted on the patient’s back, the patients can sense the needle penetration but cannot distinguish the sham acupuncture from the real one. Therefore, we believe that this method can serve as an effective placebo intervention.

Considering the trial results, both pain intensity and physical function are subjective feelings, therefore, we will use the PRO and the validated scales and questionnaires to assess the clinical outcome. For the evaluation of CS neck pain, three aspects were included in the complete assessment: neck pain, physical function, and QOL. The NPQ will be used as the primary outcome to evaluate CS-related neck pain, radiculopathy. and impairment of daily functions, while for the secondary outcomes, the MPQ will measure the pain intensity in general settings, and the SF-36 will measure patient QOL changes caused by changes in physical and mental conditions.

Salter *et al *. [12] proposed a protocol for an RCT to evaluate the effect of acupuncture for neck pain, recommending 229 cases for each arm based on the assumption of 90% power to detect a five-point NPQ difference, a 5% significance level, and a 14% drop-out rate during follow-up. In our study, a total of 945 cases are required from 9 centres, therefore, there will be 315 cases for each arm, and at least 268 cases are required to complete the trial and follow-up. The report of the study results will follow the CONSORT 2010 guidelines [13], and the operation details for acupuncture will be reported in accordance with the 2010 CONSORT-STRICTA extension [14] guidelines. Thus, this study will be able to provide high-quality evidence for the efficacy of the OAT for CS neck pain.

In conclusion, the multi-centre RCT design of this trial will be able to assess and differentiate the effects of the OAT.

## Abbreviations

ChiCtr, Chinese Clinical Trial Register; CRIVOS, Central Randomisation Interactive Voice Operating System; DME, Design, Measurement and Evaluation in Clinical Research; MPQ, McGill Pain Questionnaire; NPQ, Northwick Park Neck Pain Questionnaire; OAT, Optimized acupuncture therapy; PRO, Patient-reported outcome; SATCM, State Administration of Traditional Chinese Medicine; SF-36, The Medical Outcomes Study Short Form 36-item Health Survey.
